**Table 2 Tab2:**
[figure not shown]
Study procedures

#### Safety assessment

Each patient will undergo hematological and biochemical investigations (FBS, FBC, ESR, AST/ALT, and serum creatinine/GFR), urine full report before and after the interventions, which are done primary for safety assessment.

All adverse events experienced by patients will be recorded weekly by the investigators at every visit to the clinic. Further, patients will be advised to record any adverse reactions in their patient diaries and will be advised to inform the investigators using the given contact numbers. They will also be advised to come to the clinic for assessment when they have any unexpected symptoms or complaints. If any serious adverse events occur, they will be carefully assessed and reported to the ERC of IIM and Medical Faculty within 5 working days. No serious adverse reactions are expected with any of the three study medications. However, in the events of an adverse reaction requiring in-hospital management, the facilities and expert management would be provided and the complete clinical trial will be terminated prematurely if there is evidence that the safety of the trial participants can no longer be assured or new scientific information arises during the course of the clinical trial regarding patient safety.

### Data handling, record keeping, and dissemination

An individual file for each participant will be used to archive a hard copy of the case record forms including informed consent, results of the hematological and biochemical investigations, results of the physical examinations, and completed questionnaires. Data will be entered by a minimum number of dedicated staff and saved in a dedicated computer with password protection. These data will be retained with the researchers and will not be handed over to any other party under any circumstances. The study participant’s information will be securely stored at each clinic visit during the study. At the end of the study, all records will continue to be kept in a secure location for a 2-year period.

Study participants’ data will be stored at the department of Dravyaguna Vignana, IIM, which will be used for statistical analysis and scientific reporting. Each participant’s contact or identifying information will be separately stored. Individual participants and their research data will be identified by a unique study identification number. At the end of the study, all study databases will be de-identified and archived. A data safety monitoring board has been appointed according to the guidelines of Ethics Review Committee of Faculty of Medicine for safety monitoring. The board consists of three independent expert members. Further, we have not planned the auditing of this clinical trial, because it is a single-center trial involving only 210 patients. The results of the study will be used for scientific reporting in conferences and will be published in peer-reviewed journals. Further results of the study and the grouping information of the participants will be provided to the individual after completion of the trial.

### Ethical considerations

The approval of the research protocol has been obtained from the Research approval committee of the Faculty of Graduate Studies, University of Colombo and the Ethics Review Committees of Institute of Indigenous Medicine (IIM) and Faculty of Medicine, University of Colombo. The trial was registered in ISRCTN registry (Trial number ISRCTN18149439 10.1186/ISRCTN18149439). The study will be conducted adhering to Good Clinical Practice (GCP) guidelines. Protocol modifications will be informed to Ethics Review Committees and the trial registry for their approval.

Patients will be provided with an information sheet with the details of the research given in all three languages (Sinhala/Tamil/English) and written consent will be obtained before participation. The information provided will include the nature, duration, and possible consequences of the trial. A patient may withdraw his or her consent to participate in this study at any time, with no penalty or effect on medical care or loss of benefits. The questionnaire will be interviewer-administrated and anonymous. A minimal amount of data needed to assess the socio demographic data will be gathered. This will include occupation and nature of health condition. Researchers will not collect any other personal data.

## Method of data analysis

For primary and secondary outcome measures, the mean values at baseline and at the end of the study and the mean differences will be compared between the three arms using ANOVA (analysis of variance) or the non-parametric Kruskal–Wallis test, depending on the normality of the data. Within each treatment arm, the difference in primary and secondary outcome measures before and after the intervention period will be compared using paired-sample *t* test or non-parametric Wilcoxon signed-rank test, depending on the normality of the data. 95% confidence intervals will be calculated for all outcome measures that are normally distributed. Categorical variables will be compared between groups using the Chi-square test. Possible confounders will be adjusted using ANCOVA. Following adjustment for confounding using ANCOVA, adjusted mean values with confidence intervals will be calculated and reported. Statistical analysis will be performed using the SPSS Statistical Package program (ver. 18.0), and the level of significance will be established at α = 0.05. Missing data at outcome assessment will be replaced with the available latest values of the outcome measure. Intention-to-treat analysis will be performed for all efficacy outcomes and safety outcomes. In addition, per-protocol analysis will be performed for the efficacy outcomes by including only the patients completing the follow-up.

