## Methods

### Study design

This is a three-arm, open-label non-inferiority randomized controlled clinical trial that will be conducted at the National Ayurveda Teaching Hospital in Colombo, Sri Lanka. TMD12, used in traditional Ayurveda, and its freeze-dried formulation will be the test products. The efficacy and safety of the two Ayurvedic dosage forms will be tested against the antihistamine loratadine. Patients with symptoms of AR will be allocated randomly into the three arms after a 1-week run-in period and the medications given orally for 28 days. This study protocol was developed as required by the Standard Protocol Items: Recommendations for Interventional Trials (SPIRIT) (Additional file 1).

Ethics approval has been obtained from Ethics Review Committee, Institute of Indigenous Medicine (ERCIIM), University of Colombo, Sri Lanka (ERC 18/76) and the Ethics Committee of the Faculty of Medicine, University of Colombo, Sri Lanka (EC-18-090). The trial was registered in the ISRCTN registry (Trial number ISRCTN18149439) (Additional file 2).

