### Sample size

Sample size was calculated based on the primary outcome measurement of TNSS and as for a non-inferiority clinical trial. This study is designed to evaluate the comparative clinical efficacy and safety of two Ayurvedic dosage forms with the antihistamine loratadine, assuming non-inferiority-between the three interventions. Sample size was calculated as specified by Hampel et al. [11]. According to a previous study done among patients with allergic rhinitis using loratadine, clinically significant standardized effect sizes of TNSS are reported in the range of 0.57 to 0.67 [11]. Therefore, a standardized effect size of 0.5 was considered as the non-inferiority margin using the effect reported by Hampel and team.

Sample size was calculated for a significance level (**α**) of 5% and power of 80%. The sample size calculated using these values is 64 per group. With an expected dropout rate of 10%, minimum sample size was calculated as 70 for one arm.

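### The trial is designed and sized for non-inferiority, but the stated primary comparison is an omnibus test of difference, and no planned confidence interval is tied to the 0.5 SD margin

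*Protocol article*

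**What the plan says.** The Study design section states: "This is a three-arm, open-label non-inferiority randomized controlled clinical trial". The Sample size section carries this through: "Sample size was calculated based on the primary outcome measurement of TNSS and as for a non-inferiority clinical trial", and "a standardized effect size of 0.5 was considered as the non-inferiority margin". With a 5% significance level (sidedness not stated) and 80% power, it reports: "The sample size calculated using these values is 64 per group". This is raised to 70 per arm for 10% dropout.

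The Method of data analysis section sets out how the outcomes will be compared. For primary and secondary outcomes alike, "the mean values at baseline and at the end of the study and the mean differences will be compared between the three arms using ANOVA", or Kruskal–Wallis if the data are not normal, at a 0.05 level. It adds:

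- paired before-and-after tests within each arm;
- chi-square tests for categorical variables;
- ANCOVA for possible confounders, reporting adjusted means with confidence intervals;
- interval estimates more generally: "95% confidence intervals will be calculated for all outcome measures that are normally distributed";
- intention-to-treat and per-protocol analyses of efficacy.

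The section does not mention the margin, a contrast of either test product with loratadine, or a rule for concluding non-inferiority.

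**The concern.** A non-inferiority claim needs evidence that the deficit of each test product against loratadine is smaller than the margin. The named test has a different null hypothesis, namely that all three arms are equal. Rejecting it does not say which arms differ or in which direction. Failing to reject it does not bound any deficit. It also mixes the two questions the trial asks, decoction versus loratadine and freeze-dried product versus loratadine, into one result.

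The within-arm tests do not fill the gap. There is no placebo arm, and patients enter only with TNSS above 6, so scores may fall in every arm whatever the treatment does.

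At stake is the trial's central conclusion. Without a rule tied to the margin, a reader or author could take a non-significant p-value as showing non-inferiority. That reading becomes easier to reach as the trial yields less information.

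**Working it through.** **Inputs.** From Sample size: margin 0.5 SD, power 80%, alpha 5%, 64 per arm before dropout. From Method of data analysis: three-arm ANOVA at 0.05. Assumptions of this check: normal data, equal SDs, SD scaled to 1, higher score is worse.

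**1. The plan's own figure.** Non-inferiority sample size per arm, true difference zero, one-sided 2.5%:

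n = 2(z₀.₉₇₅ + z₀.₈₀)² / margin² = 2(1.960 + 0.842)² / 0.5² = 62.8, so 63. The t-based version gives 63.8, so 64.

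The stated 64 reproduces. A two-sided 5% difference test to detect 0.5 SD gives the same number, so the figure does not reveal which test was intended. One-sided 5% gives 50 (t-based 51) and does not match.

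**2. ANOVA when a product is worse by the full margin.** The statistic follows a noncentral F with 2 and 189 degrees of freedom, critical value 3.04, and noncentrality λ = n Σ(μᵢ − μ̄)².

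- One product worse, means (0, 0, 0.5): Σ = 2(1/6)² + (1/3)² = 0.1667; λ = 64 × 0.1667 = 10.67; P(non-significant) = 16.5%.
- Both worse, means (0, 0.5, 0.5): the same λ, so 16.5%.
- One worse by 0.5 and the other by 0.25: Σ = 0.125; λ = 8.0; P(non-significant) = 29.0%.
- One or both worse by 0.5, at other sizes: 20.6% with 58 per arm, 13.1% with 70 per arm.

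**3. Interval versus margin in the same situations.** The rule passes a product if the upper 95% limit of (product − loratadine) is below 0.5, with pooled variance. Standard error = √(2/64) = 0.177. Simulated results at 64 per arm:

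- A product exactly at the margin passes wrongly in 2.5% of trials.
- With both at the margin, both pass in about 0.5%, and at least one passes in about 2.5 + 2.5 − 0.5 = 4.5%.

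**4. All arms truly equal.** ANOVA is non-significant in 95% of trials. The interval rule passes each product in about 80%, but both in only about 69%. In about 28% of trials ANOVA would be non-significant without non-inferiority having been shown for both.

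**5. Both products truly better by 0.5 SD.** ANOVA is significant in about 84% of trials, although both products meet non-inferiority in over 99.9%.

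Steps 2 to 5 show that neither a significant nor a non-significant ANOVA answers the non-inferiority question.

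**The case against.** The strongest reply is that this is a condensed article, and that pairwise contrasts and the formal decision rule belong in an analysis plan that is not shown. Silence on those would indeed be no finding. But the article is not silent. It names the comparison for the primary outcome, and the one it names tests a different hypothesis from the one it declares and sizes for. That mismatch stands on the text.

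Several stronger readings are tempting and are not supported:

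- **That nothing planned could ever show non-inferiority.** Confidence intervals and ANCOVA-adjusted means are planned, and a difference with its interval can be derived from the same ANOVA or ANCOVA model. What is missing is the instruction to form that contrast and compare it with the margin.
- **That the margin becomes unusable if the data fail a normality check.** The Kruskal–Wallis route brings no interval, and the general sentence on intervals is limited to normally distributed outcomes. The ANCOVA sentence has no such condition.
- **That a non-significant p-value will be counted as success.** The article states no such rule. The 16.5% is the error rate of a misreading that the plan leaves open; it is not a property of a rule the plan adopts.
- **That 16.5% and 2.5% compare like with like.** The first is a single omnibus result covering both products and the second is per comparison. The gap remains against the joint figures of 4.5% for at least one and 0.5% for both.
- **That ANOVA-based results can support no claim at all.** A significant pairwise contrast favouring a test product could legitimately support superiority. The restriction needed concerns non-significant p-values and within-arm tests.

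**Conclusion.** The concern holds in this limited form: the declared hypothesis and the stated primary comparison do not match, and no planned interval is connected to the margin, so the article does not define how non-inferiority will be concluded. If a non-significant ANOVA were read as non-inferiority, a deficit of the full margin would go undetected in about one trial in six at the planned 64 per arm. The sizes rest on normal data, equal SDs, the stated 0.5 SD margin and complete data on 64 per arm. The mismatch itself rests on the text alone and does not depend on those assumptions. It should be corrected before the data are analysed. The Trial status section says recruitment is still in progress.

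**What to change.** Rewrite the primary analysis in Method of data analysis as follows.

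- For decoction versus loratadine and, separately, freeze-dried product versus loratadine, estimate the TNSS difference from the ANOVA or ANCOVA model with a two-sided 95% confidence interval.
- Name one primary time point. The Primary outcome section lists day 28 and the ends of two follow-up months, while the analysis section refers only to the end of the study.
- Express the margin in TNSS points, or give the SD that converts 0.5 into points. The article gives neither, so the rule cannot yet be applied to a TNSS difference.
- Conclude non-inferiority for a product only if the interval limit unfavourable to it lies inside the margin, in both the intention-to-treat and per-protocol sets, whatever the normality check shows. Add a bootstrap interval as a sensitivity analysis.
- State that a non-significant ANOVA or Kruskal–Wallis p-value, and the within-arm paired tests, cannot support a non-inferiority claim.

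The cost is rewording; no new data or patients are needed for each comparison taken singly. The 64 per arm gives about 80% power per comparison at one-sided 2.5%, but only about 69% to show both products non-inferior when all arms are equal. The sample size section should say so and should state the one-sided level.

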## Abstract

**Background:**

Allergic rhinitis (AR) is an immune response of the nasal mucosa to airborne allergens and involves nasal congestion, watery nasal discharge, itching of the nose, and sneezing. The symptoms of allergic rhinitis may significantly affect a patient’s quality of life and can be associated with conditions such as fatigue, headache, cognitive impairment, and sleep disturbances. Various complementary and alternative medicine treatments have been used for this condition in clinical practice. The Ayurveda system of medicine is the most common complementary medicine system practiced in Sri Lanka. The aim of this study is to examine the efficacy and safety of a decoction used in traditional Ayurveda for allergic rhinitis and its ready- to-use freeze dried formulation in comparison to an antihistamine over a period of 4 weeks on relief of symptoms in allergic rhinitis.

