**Study design:**

This is a three-arm, open-label, non-inferiority, randomized controlled clinical trial enrolling patients with AR. Tamalakyadi decoction containing 12 ingredients (TMD12), used in traditional Ayurveda and its freeze-dried formulation are the test products. The efficacy and safety of the two Ayurvedic dosage forms will be tested against the antihistamine loratadine. Patients with symptoms of AR will be allocated randomly into the three arms after a 1-week run-in period and the medications will be given orally for 28 days. Total Nasal symptom Score (TNSS) of the patients will be used as the primary efficacy endpoint. TNSS will be recorded and compared between the three arms prior to visit 1, at the end of 28 days, and end of the first and second months of follow-up. Symptom scores of daytime nasal symptoms, night time nasal symptoms, non-nasal symptoms and health-related quality of life questionnaire are used as secondary end points.

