### Outcome measurements

#### Primary outcome

TNSS of the patients will be used as the primary efficacy endpoint, which has been previously used in allergic rhinitis clinical trials. The mean difference in TNSS will be compared between the three arms at baseline and at the end of 28 days, end of the first month of follow-up and second month of follow-up. The TNSS assesses the symptoms of watery rhinorrhea, nasal obstruction, sneezing, and nasal itching on a four-point scale. The total score range from 0 to 12 where 0 = absent symptoms (no sign/symptom evident), 1 = mild symptoms (signs/symptoms clearly present, but minimal awareness; easily tolerated), 2 = moderate symptoms (definite awareness of signs/symptoms that are bothersome but tolerable), 3 = severe symptoms (signs/symptoms that are hard to tolerate; causes interference with activities of daily living and/or sleep).

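### The visit that decides the primary TNSS comparison is not fixed, and the sections disagree; if an off-treatment visit decides, the trial may lose its ability to detect inferiority

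*Protocol article*

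**What the plan says.** - **Aim (Abstract, Background).** Efficacy and safety are to be examined against an antihistamine "over a period of 4 weeks on relief of symptoms in allergic rhinitis". The Methods give treatment for 28 days.
- **Abstract, Study design.** TNSS is recorded and compared between arms "prior to visit 1, at the end of 28 days, and end of the first and second months of follow-up".
- **Primary outcome.** "TNSS of the patients will be used as the primary efficacy endpoint", and the mean difference is compared between arms "at baseline and at the end of 28 days, end of the first month of follow-up and second month of follow-up". No visit is ranked above another.
- **Method of data analysis, between arms.** For primary and secondary outcomes the arms are compared on "the mean values at baseline and at the end of the study" and on the mean differences. The closing time point is not defined.
- **Method of data analysis, within arms.** The next sentence tests change "before and after the intervention period", which is a different term. The per-protocol set in the same section is limited to patients who finish follow-up.
- **Secondary outcomes.** For quality of life, the end of the intervention is explained as 4 weeks plus both follow-up visits, so the terms for time are used loosely.

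**The concern.** A 4-week aim points to day 28. The outcome section allows three visits. The analysis section points, on its literal reading, to the last of them, two months off treatment. These cannot all describe one primary comparison.

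The choice matters more here than in a superiority trial. There, reading the outcome after drug effects have faded costs power. In a non-inferiority trial it helps the claim, because arms that have drifted back together look alike whatever happened on treatment. A product clearly worse than loratadine while both were being taken could then be called non-inferior. With no visit ranked first, the visit could also be chosen once results are known, and the trial is open-label.

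**Working it through.** **Inputs.** From the Sample size section: margin 0.5 SD, alpha 5% (sidedness not stated), power 80%, 64 per group, and reported TNSS effect sizes of 0.57 to 0.67 in a loratadine study. Assumed here: a pairwise one-sided non-inferiority test with the same SD at every visit.

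**Step 1: reproduce the plan's figure.** With a true difference of 0,

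n = 2(z0.975 + z0.80)² / 0.5² = 2(1.960 + 0.842)² / 0.25 = 62.8, so 63 per group.

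The exact t-based calculation gives 64, with power 80.1%. The stated 64 is therefore reproduced at one-sided 2.5%. One-sided 5% would give 50 (51 by t), which does not match, so 2.5% is used below.

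**Step 2: chance of passing as the arms converge.** Let D be the true deficit against loratadine, in SD units, at the visit that decides. The standard error is √(2/64) = 0.1768, and

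P(pass) = Φ((0.5 − D)/0.1768 − 1.96).

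Take a product exactly at the margin, 0.5 SD worse, at day 28:

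| Deficit persisting at the deciding visit | D | Φ argument | P(pass) |
|---|---|---|---|
| All (as at day 28) | 0.5 | 0 − 1.96 = −1.96 | 2.5% |
| Half | 0.25 | 1.414 − 1.96 = −0.546 | 29% |
| A quarter | 0.125 | 2.121 − 1.96 = 0.161 | 56% |
| None | 0 | 2.828 − 1.96 = 0.868 | 81% (80.1% by t) |

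The last row is simply the design power.

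**Step 3: the same check for an inert product.** Assume that the 0.57 to 0.67 range is loratadine's effect over no treatment in this population. The inert product then passes 0.2% to 0.9% of the time at day 28, 15% to 23% if half of loratadine's effect remains (D = 0.285 to 0.335), 46% to 53% if a quarter remains (D about 0.14 to 0.17), and about 80% if none remains.

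**Step 4: if success at any of the three visits counted.** For one product at the margin at all three visits, each tested at one-sided 2.5%, simulation gives an error of 6.8%, 6.3% and 5.5% for assumed between-visit correlations of 0.3, 0.5 and 0.7. That is about 5% to 7% instead of 2.5%.

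Steps 2 and 4 describe different situations (deficit fading, and deficit constant), so their figures must not be added together.

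**The case against.** The strongest reply is that this is loose wording, not a decision to read the endpoint late. The closing time point in the analysis section is undefined, the aim is set at 4 weeks, and the within-arm tests span the intervention period. The authors may have meant day 28 throughout, and an analysis plan not shown may say so. This stands in part. A reader might infer that the protocol fixes the primary comparison at two months after treatment, but it does not. That is only the literal reading, supported by the contrast with the intervention period and by the per-protocol definition. The conflict between sections remains, however, and a later plan could choose any of the three visits and still claim to follow the protocol.

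A second reply is that nothing in the document says how long either treatment's effect lasts. This also stands. A reader might conclude that non-inferiority at month 2 is almost automatic. Even with complete convergence, about one comparison in five fails, and with partial persistence the pass rate is much lower.

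Third, a reader might count two products at three visits as six chances of success. The document states no rule that success at any visit suffices, and its named between-arm test is a three-arm ANOVA or Kruskal–Wallis test. The any-visit error in Step 4 is a risk left open by the missing ranking, not a stated procedure.

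**Conclusion.** The point holds as an unresolved conflict about the deciding visit. That no visit is designated primary, and that the aim, outcome and analysis sections disagree, is certain from the text. That month 2 was intended is not established.

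The consequence depends on persistence of effect. For a product 0.5 SD worse at day 28, the chance of a false non-inferiority finding goes from 2.5% to about 29%, 56% or 80% as half, a quarter or none of the deficit remains. These figures rest on a margin of 0.5 SD, 64 per group, one-sided 2.5%, a constant SD and assumed persistence. The direction is not in doubt: any convergence after treatment favours the claim. Because the choice of visit can reverse the conclusion, it should be settled before comparative results are seen.

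**What to change.** Name TNSS at day 28 (end of treatment) as the single primary time point in the Abstract's Study design paragraph, in Primary outcome and in Method of data analysis. In the last of these, replace the end-of-study wording with day 28 for the primary between-arm comparison. Keep the month 1 and month 2 scores as secondary measures of persistence of effect, with no non-inferiority claim attached.

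The cost is a protocol amendment submitted to the ethics committees and the registry, as Ethical considerations requires, while recruitment is in progress. Follow-up results could no longer carry the primary claim. The sample size does not change, because the margin, alpha and power do not depend on the visit, and no visit is added or removed.

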### Participants

Patients will be selected from those seeking treatment for allergic rhinitis. Participation in this research project is voluntary. Patient recruitment is done by screening for eligibility criteria (inclusion and exclusion criteria). Eligible subjects will be randomly assigned to the TMD12 decoction group, TMD12 freeze-dried group (TMD12-FD) or the antihistamine, loratadine group.

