### Inclusion and exclusion criteria

The inclusion criteria include (1) age group of 18–65 years at the time of enrollment, of either sex; (2) presence of two or more nasal symptoms (watery rhinorrhea, nasal obstruction, sneezing, and nasal itching); (3) Total Nasal Symptom Score (TNSS) > 6 (0 = no symptoms, 1 = mild symptoms, 2 = moderate symptoms, 3 = severe symptoms); (4) have given written, informed consent to participate in this study.

The exclusion criteria include: (1) Patients with deviated nasal septum/ nasal polyps/ nasal growth/ adenoids/ asthma; (2) Patients with impaired liver and kidney functions, anemia, and unstable cardiovascular conditions or cerebrovascular conditions; (3) currently or previously treated for any malignancy; (4) patients on steroid therapy; (5) already on treatment with TMD12 decoction or antihistamines; (6) pregnant or lactating mothers; (3) those who have known systemic disorders; (4) those who have any history of drug allergy to any of the investigational products; (7) illiterate patients without a literate relative/guardian who can explain the procedures and maintain the patient diary, (8) and any other patients who are considered unsuitable for recruitment by the investigators.

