#### Secondary outcomes

The following four symptom scores will be used as secondary end points.
Mean score of daytime nasal symptomsMean score of night time nasal symptomsMean score of non-nasal symptomsPatient’s self-rated symptom scores (daily rhinitis diary card) and allergic rhinitis grading symptoms will be used as secondary measures of the efficacy in the clinical trial. Such symptom scores will be collected on a weekly basis during the assessment period. The measurement of symptoms on a four-point rating scale with the following definitions will be used.
= absent symptoms (no signs/symptoms evident)= mild symptoms (signs/symptoms clearly present, but minimal awareness; easily tolerated)= moderate symptoms (definite awareness of signs/symptoms that are bothersome but tolerable)= severe symptoms (signs/symptoms that are hard to tolerate; causes interference with activities of daily living and/or sleep).Mean score of health-related quality of life score – Health-related quality of life is measured using allergic rhinitis symptoms at the baseline and end of the intervention (after 4 weeks, 1 month of follow-up, and 2 months of follow-up).

Changes in the serum IgE level and eosinophil count will be studied by comparing before and after treatment values. Procedures related to the study are shown in Table 2.

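### Within-arm before/after tests are planned at alpha 0.05 without being labelled descriptive, although in this design they cannot separate a drug effect from regression to the mean, natural course or expectation

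*Protocol article*

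**What the plan says.** Method of data analysis plans two kinds of comparison for the primary and secondary outcomes. The first is between arms: ANOVA or Kruskal-Wallis on baseline values, end-of-study values and mean differences, with ANCOVA for possible confounders. The second is within arms: "Within each treatment arm, the difference in primary and secondary outcome measures before and after the intervention period will be compared using paired-sample" t tests or the Wilcoxon signed-rank test. The 0.05 significance level is set for the whole section, and nothing ranks the second kind below the first.

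Four other places matter:

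- Inclusion and exclusion criteria: patients enter with "Total Nasal Symptom Score (TNSS) > 6". Primary outcome uses the same scale as the endpoint: "The total score range from 0 to 12".
- Study design: a "three-arm, open-label non-inferiority randomized controlled clinical trial", with patients "allocated randomly into the three arms after a 1-week run-in period and the medications given orally for 28 days".
- Participants: "Eligible subjects will be randomly assigned to the TMD12 decoction group, TMD12 freeze-dried group (TMD12-FD) or the antihistamine, loratadine group". All three arms receive an active or test product.
- Secondary outcomes: "Changes in the serum IgE level and eosinophil count will be studied by comparing before and after treatment values".

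On timing, Recruitment has the baseline TNSS form completed together with the eligibility work-up, and the Abstract places the first TNSS before visit 1. The readable text mentions no second baseline after the run-in. The procedures table (Table 2) could not be read in the copy reviewed.

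**The concern.** A before/after change within one arm is the sum of any drug effect and everything else that moves the score. Three such influences are built into this design. Patients are admitted because their TNSS is high, so a later score tends to be lower even if nothing is done. Rhinitis symptoms fluctuate, and people seek treatment when they are bad. Patients know what they are taking and rate their own symptoms, so expectation can contribute. Without a placebo or untreated arm, nothing in the trial measures these components, and a paired test attributes the whole change to the period on treatment.

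The trial is meant to supply evidence on products that, according to the Background, have no published efficacy study. Paired tests at alpha 0.05 in each arm, with no stated role, leave it open for a significant within-arm fall to be reported as an efficacy result.

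**Working it through.** **1. The plan's own sample size.** Sample size gives a standardised margin of 0.5, alpha 5%, power 80% and 64 per group. With one-sided 0.025 (equivalently two-sided 0.05), n = 2 × (1.96 + 0.842)² / 0.5² = 62.8, so 63; the t-based calculation gives 63.8, so 64. This reproduces the plan. One-sided 0.05 would give 50. For dropout, 64 × 1.1 = 70.4, against the stated 70.

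**2. How small a fall is significant within an arm.** A paired t test with n = 64 is significant once the mean change reaches t(0.975, 63) / √64 = 1.998 / 8 = 0.25 SD of the change. It has 80% power at 0.36 SD.

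**3. The fall from selection alone.** If the entry score is also the baseline, the expected fall is roughly (1 − ρ) × (mean baseline of those admitted − source mean), where ρ is the test-retest correlation. For an assumed source mean of 7, SD 2.5 and ρ = 0.7, those scoring above 6 have a mean baseline of 8.67, so the fall is about 0.3 × 1.67 = 0.50. Simulation with scores rounded and bounded to 0-12 gives 0.53, with an SD of change of 1.83. The ratio is 0.53 / 1.83 = 0.29, above the 0.25 threshold.

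**4. Chance that an inert arm shows a significant fall.** Simulated, n = 64, two-sided 0.05, SD 2.5, entry score used as baseline. The nominal rate in this direction is 2.5%. Source mean, SD and ρ are assumptions, since the protocol gives none of them.

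| Source mean | ρ = 0.5 | ρ = 0.7 | ρ = 0.8 |
|---|---|---|---|
| 7 | fall 0.87, 86% | fall 0.53, 63% | fall 0.36, 46% |
| 8 | fall 0.59, 54% | fall 0.36, 35% | fall 0.25, 24% |
| 9 | fall 0.37, 27% | fall 0.23, 18% | fall 0.15, 13% |

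Over source means 6.5 to 9, SD 2 to 2.5 and ρ 0.5 to 0.8, the chance runs from about 8% (mean 9, SD 2, ρ = 0.8) to about 94% (mean 6.5, SD 2.5, ρ = 0.5, fall 1.02).

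**5. If baseline is measured again after the run-in.** Selection then acts on a score that is not part of the before/after difference. The chance drops to about 2% to 3%, which is nominal.

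**6. Separate baseline plus a non-specific improvement.** With source mean 7, SD 2.5 and ρ 0.5 to 0.7, an assumed 0.5-point fall from natural course or expectation gives 35% to 52%, and a 1-point fall gives 87% to 98%. Over the wider range of step 4, a 1-point fall gives about 86% to 100%.

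**The case against.** The strongest reply is that the plan does not rest on these tests. The Abstract and the Primary outcome section define the primary comparison as TNSS between the three arms, the trial is framed as non-inferiority to loratadine, and the between-arm analysis is listed first. Regression to the mean acts alike in randomised arms, so that comparison is not biased by it. All of this stands. A reader might infer that the sponsor intends to claim efficacy from the paired tests, but no section says so.

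Second, there is a one-week run-in. If baseline is taken after it, the selection effect all but disappears (step 5). The Recruitment section points to a baseline taken with the eligibility work-up, but Table 2 could settle this and was not readable. So a reader might infer that a significant improvement is likely for any inert product; the documents do not support that without inputs they do not give.

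Third, one might read the IgE and eosinophil sentence as allowing only a before/after comparison. It stands under Secondary outcomes, however, and the analysis section applies ANOVA or Kruskal-Wallis between arms to secondary outcome measures, so the between-arm test appears to cover both. Nobody is selected on IgE or eosinophils either, so the entry-threshold argument hardly reaches them.

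Finally, confidence intervals and ANCOVA are already planned. That is true, but baseline is not named as the covariate and the within-arm tests are given no limited role.

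**Conclusion.** The point holds, within limits. The protocol commits to within-arm tests at alpha 0.05 on the primary and secondary outcomes, and in an open-label trial with a symptom threshold for entry and no placebo or untreated arm their p-values cannot show efficacy. That conclusion needs no assumed figure. How often they would mislead does: about 8% to 94% with the entry score as baseline, about 2% to 3% with a separate post-run-in baseline, and about 86% to 100% if a 1-point non-specific improvement is added to the latter. These figures are for TNSS; other outcomes are affected by the threshold only as far as they correlate with it. The defect lies in the unstated role of the tests, not in the randomised comparison. It is worth correcting, and it does not undermine the primary analysis.

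**What to change.** In Method of data analysis, replace the within-arm testing sentence with three statements:

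- Within-arm mean change is reported with its 95% CI as description only, and paired-test p-values are not used as evidence of efficacy. The label is needed because an interval for change that excludes zero says the same as the paired t test.
- Efficacy conclusions rest on between-arm differences from ANCOVA with the baseline value of the outcome as covariate, with confidence intervals. This includes IgE and eosinophils as secondary outcomes.
- For TNSS, that interval is compared with the stated non-inferiority margin. The margin is given as 0.5 in standardised units, so interval and margin must be put on one scale.

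The text should also say whether the baseline TNSS is the entry score or one taken after the run-in.

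The cost is wording only: no additional patients, visits or data. The one loss is that within-arm p-values are no longer reported as efficacy results.
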